### Phase 2: ASSIST-ICU Pragmatic Trial Design

The ASSIST-ICU pragmatic trial will use a prospective, nonrandomized, 2-unit pretest-posttest design. The specific components of the ASSIST-ICU CDSS and how the implementation will be operationalized, implemented, measured, and monitored for feasibility will be incorporated into the research protocol at the end of phase 1.

#### Study Setting and Participants for Pragmatic Trial

This study will take place at University of Iowa Health Care. Within University of Iowa Health Care, we will include 2 adult ICUs. Both units have implemented comprehensive patient physical activity programs that include protocol-based activity progression, routine PT consultation on ICU admission, and standardized activity assessment and intervention documentation for RNs and PTs in the EHR. The ASSIST-ICU CDSS will include 2 participant groups: clinicians and patients. The clinicians will include all RNs and PTs working in the selected adult ICU units. RN-to-patient ratios in the ICUs are typically 1:2, and PTs usually manage 6 to 8 patients per day. Patients will include all adults admitted to a participating ICU for at least 24 hours. As a pragmatic trial focused on decision-making at the point of care, we will not place restrictions on age, comorbidities, severity of illness, or expected discharge outcomes.

#### Intervention

As the trial involves using a prospective, nonrandomized, 2-unit pretest-posttest design, the ASSIST-ICU CDSS will be implemented in each ICU for a period of 9 months using a staggered approach, with 1 ICU receiving the intervention at a time. A training period will be conducted with RN and PT end users before implementation to facilitate effective use of the ASSIST-ICU CDSS and integration into existing workflows. Training will be scheduled based on each clinician’s schedule and last approximately 15 minutes. In addition, resource materials will be distributed to each unit before and throughout the trial.

#### Data Collection and Analysis for Pragmatic Trial

Feasibility and effectiveness data will be captured via the EHR. Study data will be extracted from the EHR using EHR reports that are built from the structured data fields used to create the ASSIST-ICU CDSS. Baseline data will be collected via the reports before the intervention implementation using silent data collection. Silent data collection functionality allows CDSS logic to actively run in the system, but users do not yet have access to use the CDSS dashboard, allowing for baseline data collection.

We will evaluate key implementation and clinical outcomes by using the RE-AIM (reach, effectiveness, adoption, implementation, and maintenance) framework because it considers both the feasibility (reach, adoption, and implementation) and clinical effectiveness outcomes of the intervention (Table 3) [60].

The primary feasibility outcome will be physical activity decision-making (defined as the number of patients with out-of-bed activity documented and a corresponding CDSS designation of “safe” on a given ICU day). Secondary measures include acceptability and usability of CDSS. Acceptability (defined as the belief that an intervention is agreeable, palatable, or satisfactory [56]) and usability (defined as being appropriate for a specific context of use [55]) will be measured through online surveys. We will also evaluate potential safety events routinely reported in physical activity studies [61] and documented in the health system’s patient safety reporting system, including whether the following events occurred during out-of-bed activity: fall to the floor, unplanned extubation, or line removal requiring urgent replacement.

On trial completion, all ICU RNs and PTs who worked in a study ICU will be invited to participate in a web-based survey. Usability (SUS), cognitive workload (NASA-TLX), and acceptability (AIM) will be measured and calculated in the same manner as described for the simulated trial.

We will generate histograms and bar charts to evaluate the distributions of all variables of interest and report appropriate descriptive statistics. Continuous variables will be summarized by means and SDs or medians and IQRs, as appropriate. Categorical variables will be summarized as counts and percentages. Preexisting differences in the outcome variables at baseline will be assessed using 2-sample *t* tests, the Wilcoxon rank sum test, or the Fisher exact test. Frequencies and percentages will be calculated to determine the feasibility of participation measures. A 2-sample binomial test will be used to test the null hypothesis that decision accuracy with the support tool does not differ from accuracy without it. Unit-stratified means and SDs will be calculated for SUS, NASA-TLX, and AIM scores. *P* values will be reported, and statistical significance will be evaluated at α=.05.

**Table 3 table3:** Study outcomes by RE-AIM (reach, effectiveness, adoption, implementation, and maintenance) element.

Elements and end points		Data collection

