### Phase 2: ASSIST-ICU Simulated Trial Design

#### Overview

We will conduct a simulated trial comparing the ASSIST-ICU CDSS interface with usual care (no ASSIST-ICU interface) in a simulated EHR environment. We will operationalize evidence-based decision-making through the creation of 6 expert-validated clinical scenarios. Of the 6 simulations, 3 will meet the out-of-bed safety definition, and 3 will not. All 6 simulations will be completed by each participant in a random order generated using the RAND function of Microsoft Excel. The decisions (regarding whether out-of-bed activity is safe or unsafe) will be recorded, and the number of correct decisions (range 0-6) for each participant will serve as our outcome measure of effectiveness (Table 2).

**Table 2 table2:** Operationalization for scoring each clinical scenario.

	ASSIST-ICU^a^ CDSS^b^ recommends patient out of bed: yes	ASSIST-ICU CDSS recommends patient out of bed: no
Clinician decision to mobilize patient out of bed: yes	1	0
Clinician decision to mobilize patient out of bed: no	0	1

^a^ASSIST-ICU: Aggregating Patient Safety and Status Information to Support Time-Sensitive Interventions in the Intensive Care Unit.

^b^CDSS: clinical decision support system.

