**Effectiveness**		
	Ratio of safe alerts to total alerts	EHR report
	Primary clinical end point: time to first out-of-bed activity	EHR report
	Secondary clinical end points: highest level of activity in ICU, ICU and hospital lengths of stay, and discharge disposition	EHR report

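### The ICU trial's primary feasibility outcome is a count without a denominator, and it is not the decision accuracy that the planned binomial test names

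*Protocol article*

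**What the plan says.** All references are to the protocol article.

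- **Outcome** (Data Collection and Analysis for Pragmatic Trial). Decision-making about physical activity is labelled the primary feasibility outcome. It is a daily tally: "the number of patients with out-of-bed activity documented and a corresponding CDSS designation of" safe, taken per ICU day. Table 3 lists it under Implementation and adds no denominator.
- **Test** (same section). A 2-sample binomial test is to "test the null hypothesis that decision accuracy with the support tool does not differ from accuracy without it". The same sentence is used for the simulated trial.
- **Accuracy scoring.** The only scoring rule is Table 2, in the Overview of the simulated trial. Its columns are the CDSS recommendation, yes then no. The rows read "Clinician decision to mobilize patient out of bed: yes 1 0" and "Clinician decision to mobilize patient out of bed: no 0 1". Agreement scores 1 in either direction, and mobilising against a CDSS no scores 0.
- **Design.** The ICU trial compares periods before and after go-live in two ICUs, without randomisation. It takes all adults with an ICU stay of at least 24 hours, whatever their severity. The CDSS logic runs silently at baseline, so the designation exists in both periods.
- **Other end points.** Table 3 separately names "Primary clinical end point: time to first out-of-bed activity". Safety is tracked through reported falls and tube or line dislodgement.

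**The concern.** A binomial test compares successes out of a known number of trials. The outcome definition supplies a number of successes only, and does not say whether the trials are safe patient-days, all patient-days or patients. It also uses one cell of Table 2 (CDSS yes, clinician yes), whereas accuracy in the sense of Table 2 uses all four. An analyst who follows the definition and one who follows the test sentence would compute different quantities.

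Two consequences follow if the definition is used as written. First, the number depends on how many patients are in the unit and how many of them are designated safe. Neither is a clinician decision, and both can differ between two calendar periods in a trial without randomisation or severity limits. Second, the number takes no account of what happens to patients designated not safe, although Table 2 treats mobilising them as an error. A tool that improved selection and one that simply raised mobilisation everywhere could give the same result.

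**Working it through.** **The article's own figure.** None is given for this outcome. The only power figure, 99.2%, belongs to the simulated trial. With 25 × 6 = 150 decisions per group treated as independent, 75% against 50% correct and two-sided α = .05, a pooled z test gives 99.5% and a continuity-corrected one 99.3%. That figure stands and does not bear on this point.

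**Inputs.** The article gives no census, safe share or mobilisation rate, so these are assumptions: N = 20 patients on an ICU day, safe share s = 0.50, 40% of safe patients mobilised (m1 = 0.40), 10% of not-safe patients mobilised (m0 = 0.10).

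**Formulas.**
- Count as defined: N × s × m1
- Proportion of safe patients mobilised: m1
- Accuracy scored as in Table 2: s × m1 + (1 − s) × (1 − m0)
- Not-safe patients mobilised: N × (1 − s) × m0

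**Base day.** Count 20 × 0.50 × 0.40 = 4.0. Accuracy 0.50 × 0.40 + 0.50 × 0.90 = 0.65. Not-safe mobilised 20 × 0.50 × 0.10 = 1.0.

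**Decisions unchanged (m1 and m0 fixed).**

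| Change | Count | Change in count | Safe mobilised | Accuracy |
|---|---|---|---|---|
| Census 24 | 24 × 0.50 × 0.40 = 4.8 | +20% | 40% | 65% |
| Safe share 60% | 20 × 0.60 × 0.40 = 4.8 | +20% | 40% | 0.24 + 0.36 = 60% |
| Both | 24 × 0.60 × 0.40 = 5.76 | +44% | 40% | 60% |

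The relative change in the count is (N × s after) / (N × s before), whatever m1 is. So the assumed mobilisation rate does not matter here. A 5% or 10% change in census or in the relative safe share moves the count by 5% or 10%.

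**Decisions changed.**

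| Change | Count | Accuracy | Not-safe mobilised |
|---|---|---|---|
| m1 to 0.60 and m0 to 0.30 | 20 × 0.50 × 0.60 = 6.0 | 0.30 + 0.35 = 65% | 20 × 0.50 × 0.30 = 3.0 |
| m1 to 0.60, m0 stays 0.10 | 6.0 | 0.30 + 0.45 = 75% | 1.0 |
| m1 to 0.50, census 16 | 16 × 0.50 × 0.50 = 4.0 | 0.25 + 0.45 = 70% | 16 × 0.50 × 0.10 = 0.8 |

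The first two rows have the same count (+50%), although not-safe mobilisation triples in one and is flat in the other. In the third, a real gain leaves the count at its base value.

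**Choice of denominator.** On the base day the count is 4.0/10 = 40% of safe patients or 4.0/20 = 20% of all patients. If the safe share becomes 60%, the first stays at 4.8/12 = 40% and the second becomes 4.8/20 = 24%. A binomial test on all patient-days would therefore still respond to case mix.

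**The case against.** The strongest reply is that a proportion is plainly intended. A binomial test is named, a count of successes is its numerator, and the silent baseline run makes a denominator available. The article is a condensed account, and it says that how implementation will be measured and monitored for feasibility is to be written into the research protocol after phase 1. Much of this is fair: it would be wrong to say that the count cannot enter a binomial test. What it does not answer is that the definition and the test are both printed here and name different quantities. The implied denominator has at least two natural readings, which behave differently under a change in case mix.

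A reader might also infer more than the text supports:

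- *That the whole before-after comparison is uninterpretable.* This is the primary feasibility outcome of a pilot. The primary clinical end point is time to first out-of-bed activity, and this definition does not affect it.
- *That the count grows simply because the tool is live for 9 months.* The definition is per ICU day, and no baseline length is stated.
- *That mobilising not-safe patients is recorded nowhere.* If decision accuracy is read through Table 2, the tested quantity scores it as an error; it is the outcome definition that omits it. Harm is also monitored, although reported falls and dislodgements are not the same thing as mobilisation on a not-safe day.
- *That the Table 3 row "Ratio of safe alerts to total alerts" has to be replaced.* It contains no clinician action and mostly describes case mix, but it is neither primary nor assigned a test.

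**Conclusion.** The point holds as a definitional conflict in the primary feasibility outcome. The outcome is a count of one cell without a denominator. The test is of an accuracy that the ICU section does not define and that, under the only scoring in the article, spans all four cells.

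If the definition is followed as written, the result shifts one for one with relative changes in census and safe share. In the assumed example that is +20% for either change and +44% for both, with decisions constant. It also cannot separate selective from indiscriminate mobilisation. The direction of these effects follows from the definition alone. Their size rests on assumed inputs, because the article gives none, and nothing here shows that census or case mix will in fact differ between the periods.

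**What to change.** In Data Collection and Analysis for Pragmatic Trial:

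1. Define the primary feasibility outcome as the proportion of patient-days designated safe by the CDSS on which out-of-bed activity is documented.
2. Report beside it the proportion of patient-days designated not safe on which out-of-bed activity is documented.
3. Name these two quantities in the analysis paragraph in place of decision accuracy, and carry the same wording into the Implementation row of Table 3.

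Scoring every patient-day as in Table 2 would also reconcile outcome and test, but it is the weaker choice. In the example it falls from 65% to 60% on case mix alone, and it stays at 65% when mobilisation rises in safe and not-safe patients alike.

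The cost is mainly wording, best settled before baseline collection so that the denominator is not chosen after the data are seen. The designation is generated in both periods, and the article describes standardised activity documentation in both units, so the proportions should be obtainable. The small downside is that the EHR report must link each day's designation to that day's activity, with the designation preceding the activity where timestamps allow. The article does not say whether the planned reports do this, so it should be checked when they are built.

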### ASSIST-ICU Algorithm Development

ASSIST-ICU is a knowledge-based algorithm using discrete nursing, respiratory therapy, and physical therapy documentation to synthesize patient data with physical activity guideline recommendations. The ASSIST-ICU algorithm was developed using an iterative process involving (1) translating expert recommendations into operational definitions, (2) identifying discrete data fields in the EHR, and (3) developing logic statements for the algorithm [35]. We used an expert consensus statement on early mobility readiness and safety criteria to develop operational definitions in 4 domains: respiratory, cardiovascular, neurological, and other [36]. An example from the respiratory domain is shown in Table 1. Each domain is evaluated using 24 hours of data to score a patient’s readiness for mobility (yes or no). Overall readiness is scored as “yes” only if all domains are scored as ready for mobility; if any domain is scored as “no,” the overall readiness score is “no.”

Our team established content validation of the operational definitions [37], and retrospective testing of the decision support rules has been published [34]. The ASSIST-ICU CDSS will be delivered via an EHR tool. Initial feedback from focus groups will inform prototype development to include an icon that indicates readiness for mobility (“yes” or “no”) with the ability to drill down to the features contributing to the score, providing details on why the patient met or did not meet the readiness elements.

**Table 1 table1:** Example of algorithm development process from the respiratory domain.

Variables	Description
Expert recommendation [36]	Clinical considerations for maintaining respiratory safety with out-of-bed exercises include that an artificial airway (eg, endotracheal tube, tracheostomy tube) is not in itself a contraindication, and SpO_2_^a^ should be ≥90%
Operational definition	If a patient is receiving mechanical ventilation, the patient’s most recent SpO_2_ reading and the 24-hour average SpO_2_ reading must be ≥90%
Data fields	Medical device group=endotracheal tube or tracheostomy SpO_2_ row
Logic statement	If medical device group=endotracheal tube OR tracheostomy tube, then most recent SpO_2_ reading ≥90% AND 24-hour average SpO_2_ reading ≥90%

^a^SpO_2_: peripheral capillary oxygen saturation.

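### The ICU primary feasibility outcome depends on charting, and charting completeness may differ between the silent baseline and the live period, so a rise need not mean more mobilisation.

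*Protocol article*

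**What the plan says.** All references are to the protocol article.

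- **Outcome** (Data Collection and Analysis for Pragmatic Trial): the primary feasibility outcome is the "number of patients with out-of-bed activity documented"; a patient counts only where the tool also rates that ICU day as safe. The data come from "EHR reports that are built from the structured data fields used to create the ASSIST-ICU CDSS".
- **Flag** (ASSIST-ICU Algorithm Development): "ASSIST-ICU is a knowledge-based algorithm using discrete nursing, respiratory therapy, and physical therapy documentation". The planned display lets users drill down, "providing details on why the patient met or did not meet the readiness elements".
- **Baseline** (Data Collection and Analysis for Pragmatic Trial): "Silent data collection functionality allows CDSS logic to actively run in the system", while users cannot yet open the dashboard.
- **Go-live** (Intervention): nurses and physical therapists are trained for about 15 minutes "to facilitate effective use of the ASSIST-ICU CDSS and integration into existing workflows", and resource materials are distributed before and throughout the trial.
- **Design and test**: a nonrandomised pretest-posttest comparison in two units. The stated analysis is: "A 2-sample binomial test will be used to test the null hypothesis that decision accuracy with the support tool does not differ". The comparator is the absence of the tool.
- **Other end points** (Table 3): EHR reports also supply time to first out-of-bed activity (the primary clinical end point) and highest activity level. Safety events come from the safety reporting system.

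**The concern.** The activity half of the outcome registers only what is charted, so as worded an uncharted mobilisation does not count. The flag half is an algorithm output, but its inputs are charted too. The two periods differ in more than availability of the tool: only in the second have the people who chart been trained on a dashboard that shows them the result of charted data. If entries become more complete or more timely for that reason, the documented count rises even if no additional patient leaves the bed.

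No randomised concurrent comparison is planned that would absorb such a shift, and the article describes no independent measure of activity or of charting completeness. A higher count after go-live could therefore be more mobilisation, fuller charting or both, and the stated test cannot tell them apart. The article presents phase 2 as an evaluation of effectiveness for increasing activity interventions, and its findings are to guide a multisite trial.

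**Working it through.** **Plan's own figure.** The pragmatic trial states no sample size or power, so there is nothing to reproduce for this comparison. The only power figure, 99.2%, belongs to the simulated trial. Treating 25 × 6 = 150 decisions per group as independent, 75% versus 50% gives 99.5%, which agrees closely but has no bearing on this point.

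**Inputs.** The article gives no mobilisation rate for these units, no charting completeness and no patient-day count. All three are assumptions here. Completeness *c* means the share of mobilised days that are charted as such.

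**Formula.** Documented rate = true rate × *c*. With the true rate the same in both periods, every difference is spurious. The chance of a significant result is the normal-approximation rejection probability of a two-sided 5% test of two proportions, with days treated as independent.

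**Illustration A: true rate 50% on safe days, 1,000 patient-days per period.**

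| Completeness, before → after | Documented rate, before → after | Chance of p<.05 |
|---|---|---|
| 80% → 85% | 0.50×0.80 = 40.0% → 0.50×0.85 = 42.5% | about 21% |
| 70% → 80% | 35.0% → 40.0% | about 64% |
| 70% → 85% | 35.0% → 42.5% | about 93% |

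For the last row the difference is 0.075 and its standard error is √[(0.35×0.65 + 0.425×0.575)/1000] = 0.0217. Then 0.075/0.0217 − 1.96 ≈ 1.49, and Φ(1.49) ≈ 0.93.

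**Illustration B: true rate 29%.** This is the only activity rate in the article. It comes from an external quality improvement collaborative cited in the Introduction and is not a baseline for these units.

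| Completeness, before → after | Documented rate, before → after | 500 days per period | 1,000 | 2,000 |
|---|---|---|---|---|
| 90% → 95% | 26.1% → 27.6% | about 8% | about 11% | about 18% |
| 80% → 90% | 23.2% → 26.1% | about 19% | about 32% | about 57% |

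With unchanged completeness the rate is the nominal 5%.

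**The flag half.** Overall readiness is yes only if all domains pass. Fuller input data could let a day qualify or could expose a failed criterion. The article does not say how unpopulated fields are scored, so no direction can be assigned.

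**Would restricting to days with an entry solve it?** No. Assume true mobilisation is 50% in both periods, mobilised days are charted 90% of the time in both, and non-mobilised days 60% before and 80% after.

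- Outcome as defined: 0.50×0.90 = 45% in both periods, with no bias.
- Days with an entry: 0.45 + 0.50×0.60 = 75% before; 0.45 + 0.50×0.80 = 85% after.
- Restricted outcome: 0.45/0.75 = 60.0% before; 0.45/0.85 = 52.9% after.

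That is a spurious fall. Starting from 1,000 days per period (750 and 850 with an entry), it is declared significant about 81% of the time.

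**What bounding would show.** Take the 70% → 85% row and assume non-mobilised days are charted at the same rates, so 30% and 15% of days have no entry. Counting those days as none or all mobilised gives 35.0% to 65.0% before and 42.5% to 57.5% after. Under opposite extremes the difference runs from 42.5 − 65.0 = −22.5 to 57.5 − 35.0 = +22.5 points, so the apparent gain of 7.5 points would correctly be shown as unresolved.

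**The case against.** The strongest reply is that nothing in the article says the tool changes charting. The training is short and aimed at using the tool, with no charting instruction mentioned. Both units already have standardised activity documentation, the build relies mainly on existing fields, and silent running applies the same logic in both periods. This stands as far as it goes: a change in charting at go-live is a plausible possibility and not a documented fact. But standardisation and few new fields concern the form of the record, and silent running fixes the algorithm. None of them fixes how completely staff chart.

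Two stronger readings are tempting and are not supported. A reader might infer that activity entries themselves feed the readiness score. The algorithm section describes respiratory, cardiovascular, neurological and other readiness criteria; the shared-fields sentence hints at overlap but does not establish it. A reader might also infer that any charting shift must favour the tool. That is clear only for the activity half. Moreover, the test is worded in terms of decision accuracy. If accuracy were scored as in Table 2 of the simulated trial, newly charted activity on a day flagged not safe would lower it.

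It is also fair that this is the primary feasibility outcome of a pilot, that the outcome is a count with no stated denominator (so the rates above are one reading of it), and that measurement details are to be added after phase 1. Sensitivity analyses commonly sit in a fuller document. The point here rests on what the article does fix: the outcome definition, its source, the baseline method and the test.

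**Conclusion.** The concern holds in a limited form. As defined and compared, the primary feasibility outcome cannot separate a change in charting completeness from a change in mobilisation, and the same applies to time to first out-of-bed activity and highest activity level. The document does not show that charting will change, nor that a change would favour the tool overall.

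The size depends wholly on assumed completeness, mobilisation rate and patient-days. Across the cases shown, the chance of a significant result with no change in care runs from about 8% (90% to 95% completeness, true rate 29%, 500 days per period) to about 93% (70% to 85%, true rate 50%, 1,000 days per period). A small shift does modest harm; a shift of 10 points or more in a large sample could account for the whole result. This should be settled before silent data collection starts, because what was not charted at baseline cannot be recovered later.

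**What to change.** Keep the primary feasibility outcome as defined, and add the following to the phase 2 protocol.

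1. For every ICU day in both periods, extract two indicators: whether any activity entry exists (including entries of in bed or none), and whether the algorithm's input fields are populated.
2. Report both rates by unit and period beside the primary result.
3. Prespecify a sensitivity analysis that bounds days without an activity entry: all mobilised versus none mobilised, including opposite assumptions in the two periods. Name in advance a narrower range regarded as plausible, since the extreme bounds can be wide.
4. State that a rise will be read as more mobilisation only if it survives the plausible bounds, and apply the same caution to time to first out-of-bed activity and highest activity level.
5. Do not restrict the primary denominator to days with an entry, because having an entry may itself be affected by go-live.

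The cost is two columns in reports that are already to be built, and one analysis. The downside is that the stated effect may become less certain.

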**Reach**		
	80% of unit RNs^a^ and PTs^b^ participate in training	Unit participation logs
	90% of unit RNs and PTs participate in trial	EHR^c^ report
	80% of unit RNs and PTs complete postimplementation surveys	REDCap^d^
	100% of eligible patients receive CDSS^e^ recommendations in participating ICUs^f^	EHR report

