## Discussion

### Study Significance and Strengths

This study aims to develop and evaluate a CDSS that assists clinicians in coordinating and delivering evidence-based physical activity interventions at the point of care, with minimal extraneous cognitive workload and demonstrated feasibility of real-world trial procedures.

This study rigorously addresses the most common potential pitfalls identified with CDSSs, including usability, increased cognitive workload, usefulness, effectiveness, safety, fragmented workflows, and lack of spread, by using a novel sequence of methods to design and test the CDSS interface [29]. First, we use a UCD approach, considered a gold standard, which involves iterative evaluations with future system users to enable user perspectives to be incorporated into the system design to improve usefulness and usability [46,62-64]. Second, we use the CFIR implementation science framework during the design phase to understand barriers and facilitators to CDSS implementation [44,45]. Next, we conduct a virtual trial to establish the safety and effectiveness of the intervention in a simulated EHR environment before testing the feasibility of CDSS in real-world settings. Although UCD is widely used in health care, randomized tests of efficacy and rigorous testing of CDSSs in a pragmatic trial within a single study are rare. Furthermore, few CDSS studies apply implementation science theories to inform CDSS development and testing; however, designing with an implementation science lens can help identify additional modifiable barriers to address during CDSS design and implementation [65].

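### One survey at trial completion, with the tool used in one ICU at a time, confounds unit with time since use (or length of exposure) in the usability, workload and acceptability scores

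*Protocol article*

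**What the plan says.** The Intervention section of the protocol article has the tool "implemented in each ICU for a period of 9 months using a staggered approach, with 1 ICU receiving the intervention at a time". The section on setting and participants fixes the number of units: "we will include 2 adult ICUs".

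The section Data Collection and Analysis for Pragmatic Trial sets one survey date: "On trial completion, all ICU RNs and PTs who worked in a study ICU will be invited to participate in a web-based survey". It names three instruments: "Usability (SUS), cognitive workload (NASA-TLX), and acceptability (AIM) will be measured and calculated in the same manner as described for the simulated trial". The scores are to be summarised as means and SDs by unit, with no test of change. The Reach rows of Table 3 set a completion target: "80% of unit RNs and PTs complete postimplementation surveys".

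Baseline data in the ICUs come from EHR reports run while the tool's logic is active but hidden from users. No clinician questionnaire before implementation is described. Cognitive workload is among the phase 2 secondary objectives (Study Objectives), and the Discussion describes the tool as supporting care "with minimal extraneous cognitive workload".

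**The concern.** The survey has one calendar date, but the two units finish with the tool at different times. On the literal schedule, one group rates a tool it stopped using months earlier and the other rates a tool it has just used. A difference between the two unit means could reflect the unit, the time since use, or both, and the planned summary cannot separate them.

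The delay matters most for NASA-TLX, which the article itself describes as a rating of the workload of a particular task. Distant recall suits such a scale poorly. Staff change adds to this. Some first-ICU users may have left by the survey date, and some who joined later may never have used the tool but would still be invited as having worked in a study ICU. The Study Limitations section itself raises turnover and temporary staffing as possibilities.

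A smaller, separate issue is that NASA-TLX is planned only after implementation. SUS and AIM rate the tool and cannot have a value before it exists. Workload of mobility decisions exists with or without the tool, so a post-only score leaves open whether it rose, fell or stayed the same in the ICUs. These results are meant to inform a later multisite trial.

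**Working it through.** The article gives no figure for the interval between use and survey, so there is none to reproduce. It follows from the stated schedule.

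**Inputs**
- Units: 2 (Study Setting and Participants for Pragmatic Trial).
- Exposure per unit: 9 months, one unit at a time (Intervention).
- Survey: once, at trial completion (Data Collection and Analysis for Pragmatic Trial).
- Gap between the two periods, *g* months: not stated. Assumed range 0 to 3.

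**Literal reading: sequential use, survey at the end of the whole trial.** Count months from go-live in the first ICU.
- First ICU ends at month 9.
- Second ICU runs from month 9 + *g* to month 18 + *g*, which is the earliest trial completion.
- Lag in the first ICU = (18 + *g*) − 9 = 9 + *g*. With *g* = 0 this is 9 months; with *g* = 1, 2 or 3 it is 10, 11 or 12 months.
- Lag in the second ICU = (18 + *g*) − (18 + *g*) = 0 months.

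**Other readings**

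| Reading | Lag, ICU 1 | Lag, ICU 2 | Exposure at survey, ICU 1 | Exposure at survey, ICU 2 |
|---|---|---|---|---|
| Sequential, *g* = 0 | 9 months | 0 | 9 months | 9 months |
| Periods overlap by 3 months | 9 − 3 = 6 | 0 | 9 | 9 |
| Periods overlap by 6 months | 9 − 6 = 3 | 0 | 9 | 9 |
| First ICU keeps the tool, *g* = 0 | 0 | 0 | 18 | 9 |
| Survey at the end of each unit's own period | 0 | 0 | 9 | 9 |

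The overlap rows sit badly with the one-at-a-time wording and are shown for range only. In every row with a single survey date, the units differ in lag or in exposure. Only the last row equalises both.

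**NASA-TLX measurements before the tool, per ICU:** 0. The hidden baseline phase draws on EHR reports, which cannot supply a self-rated workload score. The simulated trial does compare NASA-TLX between groups with and without the tool, but in other clinicians and a simulated record.

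**The case against.** Four points deserve weight.

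1. *The lag is inferred.* It needs the first ICU to lose the tool after its 9 months and trial completion to mean the end of the whole trial. The article never says the tool is switched off, and the Table 3 wording on surveys could fit a separate date per unit. This stands as a limit on certainty. It does not remove the problem: if the first ICU keeps the tool, the imbalance moves from time since use to length of exposure. Only a per-unit date removes it, and that is the change proposed.

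2. *Measurement detail is deferred to the end of phase 1.* The pragmatic trial design section says so. But the survey date is already stated, so the deferral is an opportunity to correct it.

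3. *No pre-post workload comparison in the ICUs is promised.* This stands. The objective is to evaluate workload, the ICU analysis is descriptive, and the controlled comparison is in the simulated trial. A reader might infer that the workload objective cannot be met in the ICUs; the documents do not support that, because a descriptive evaluation remains possible. The baseline score is therefore an inexpensive improvement and not the repair of a broken promise.

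4. *The bias should not be overstated.* A reader might infer that half the survey data are compromised. That would need equal staffing, equal response and no staff shared between units, none of which is given; therapists covering both ICUs, if any, would have a shorter lag. Nor can one say that leavers are excluded, since everyone who worked in a study ICU is to be invited. No turnover rate is given, so the effect on the 80% completion target cannot be sized.

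**Conclusion.** The point holds in a limited form. On the literal schedule, the first ICU is surveyed 9 months or more after its period ends and the second at about 0 months, so the unit-level SUS, NASA-TLX and AIM scores confound unit with time since use. If the first ICU keeps the tool, they confound unit with exposure of at least 18 months against 9. Recall and staff change are additional weaknesses in the first ICU on the literal reading, of unknown size.

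The conclusion assumes that trial completion is a single date for both units. If the sponsor already intends a separate date for each unit, the wording needs correcting and the confounding does not arise. The missing baseline concerns NASA-TLX alone. No primary outcome, sample size or hypothesis test depends on these surveys; what is at stake is the interpretation of secondary, descriptive results.

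**What to change.** Replace the single survey date with one per unit: send SUS, NASA-TLX and AIM to each ICU at the end of its own 9-month period, and say whether the first ICU keeps the tool afterwards. This equalises lag and exposure. It does not remove other differences between the units, including calendar time. The cost is a changed send date.

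As an addition, collect the 6-item NASA-TLX once in each ICU before go-live, during the hidden baseline phase or at the planned training session of about 15 minutes. Ask clinicians to rate their usual mobility decision-making as currently practised, which keeps recall short, and report the pre-post difference descriptively by ICU. With two nonrandomised units this shows whether workload changed and cannot by itself attribute the change to the tool. The cost is a few minutes per clinician and, if paired change is wanted, a way to link each person's two responses.
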